**Table 1 Tab1:** **Definitions of peri- and post-operative complications**

**Complication**	**Definition**
Intra-operative lesion of nerves	Clinical diagnosis and/or EMG findings
Dislocation of the catheter and/or the port chamber	Radiological finding
Incompatibility of contrast agent	Any allergic reaction against a contrast agent needing medical treatment with drugs
Thrombosis	Sonographic findings and/or phlebography
Post-operative bleeding	Clinical diagnosis during reoperation
Haematoma	Clinical diagnosis, no reoperation necessary
Disconnection or breakage of the catheter	Radiological findings, findings after explantation
Extravasation of injected fluid	Radiological findings and/or clinical diagnosis
Wound infection	Clinical diagnosis, wound has to be reopened and/or antibiotic treatment
Catheter sepsis	Two or more of the following symptoms:
	Temperature over 38.3°C or under 36°C;
	Heart rate over 90 beats per minute;
	Respiration rate over 20 breaths per minute, PaCO_2_ < 32 mmHg (spontaneous breathing) or PaO_2_/FiO_2_ < 200 mmHg (mechanical ventilation);
	Total peripheral WBC count >12 G/L or WBC <4.0 G/L or >10% immature neutrophils (bands), regardless of total peripheral WBC count;
	Plasma C-reactive protein >2 SD above normal value and positive findings in bacteriology of the port catheter pike
Cutaneous necrosis	Clinical diagnosis and/or histological finding
Pinch-off phenomenon	Radiological findings and/or clinical diagnosis

EMG: electromyography; PaCO2: partial pressure of carbon dioxide; PaO2: partial pressure of oxygen; FiO2: fraction of inspiratory oxygen; mmHg: millimetres of mercury; WBC: white blood cells.

**Table 2 Tab2:** **Clavien**-**Dindo classification**

**Grade**	**Definition**
Grade I	Any deviation from the normal post-operative course without the need for pharmacological treatment or surgical, endoscopic or radiological interventions. Allowed therapeutic regimens are: drugs as antiemetics, antipyretics, analgesics, diuretics and electrolytes, and physiotherapy. This grade also includes wound infections opened at the bedside.
Grade II	Requiring pharmacological treatment with drugs other than those allowed for grade I complications. Blood transfusions and total parenteral nutrition are also included.
Grade III	Requiring surgical, endoscopic or radiological intervention.
Grade IIIa	Intervention not under general anaesthesia
Grade IIIb	Intervention under general anaesthesia
Grade IV	Life-threatening complication (including central nervous system complications)* requiring intensive care unit management
Grade IVa	Single-organ dysfunction (including dialysis)
Grade IVb	Multi-organ dysfunction
Grade V	Death
Suffix ‘d’	If the patient is suffering from a complication at the time of discharge, the suffix ‘d’ (for ‘disability’) is added to the grade. This label indicates the need for follow-up to fully evaluate the complication.

*including brain hemorrhage, ischemic stroke, subarachnoidal bleeding, but excluding transient ischemic attacks.

##### Dose rate of radiation

This is defined as the product of dose rate and area of radiation (cGy × cm^2^). The correctness of documentation will be verified by a study nurse. The exact value will be documented in the CRF on the day of intervention.

##### Skill of surgeons

Surgeons will be classified in the CRF as follows: 1 to 10, 11 to 25, 26 to 50 or >50 TIVAP implantations. Whether or not surgeons have a board certificate on the day of intervention will be documented. It will also be documented whether another experienced surgeon was called in, and instances of complex or unsuccessful primary implantation will be recorded.

### Description of trial visits

The specific data to be collected at the trial visits are presented in Table 3.

**Table 3 Tab3:** **Data to be collected at trial visits one to three**

**Visit**	**1**	**2**	**3**
	**Screening**	**Day of operation**	**Post-operative day 30**
Inclusion and exclusion criteria, and written informed consent	**X**		
Baseline demographic data	**X**		
Randomisation		**X**	
Primary endpoint		**X**	**X**
Tolerability of intervention		**X**	**X**
Duration of procedure		**X**	
Primary success rate		**X**	
Survival			**X**
Complications		**X**	**X**
Serious adverse events		**X**	**X**

#### Visit one

If a subject is included, the following baseline data will be recorded in the CRF: gender, age (years), height (cm), weight (kg), relevant comorbidities (chronic obstructive pulmonary disease, lung emphysema or asthma), underlying malignant disease necessitating TIVAP, current antibiotic treatment, current CHT, smoking status, alcohol abuse, Karnofsky score.

#### Visit two

Prior to the surgical intervention, patients will be randomised to either the open or closed strategy, and the treatment assignment will be documented. Furthermore, the following details will be documented: performed intervention (SCD or PSV), surgeon’s expertise, duration of procedure, site of TIVAP implantation, primary success rate, rate of pneumothorax and haemothorax (primary endpoint), serious adverse events (SAE), study port implanted (yes or no), peri-operative prophylactic antibiotics given (yes or no), exact documentation of the executed procedure and rating of tolerability of intervention.

#### Visit three

Patients will be called by a study nurse on day 30 post-operation and asked about SAE and primary and secondary endpoints by means of a standardised questionnaire. All data will be documented in the CRF.

### Safety aspects

In the PORTAS-3 trial only SAEs meeting one of the following criteria will be documented: resulting in death, is immediately life-threatening, requiring or prolonging hospitalisation, resulting in persistent or significant disability or incapacity and other substantial medical reasons.

From the day the patient has been randomised until the regular end of trial at 30 days follow-up, or until premature withdrawal of the patient, all SAE will be documented on an SAE form, available in the investigator site file. Assessment of SAE will be based on surgical findings and the clinical course of the patient, and will be carried out by the investigators at the participating trial centres. They will be furnished with written recommendations on how to assess the causal connection with trial interventions. An SAE will have to be reported to the principal investigator by the attending physician within 24 hours after it becomes known.

#### Study-specific serious adverse events

As it can be anticipated that many events fulfilling the SAE criteria will be caused by the underlying disease or treatment and will not be related to trial intervention (for example, hospitalisation due to neutropenic fever after CHT), only SAEs not related to the underlying disease or treatment will have to be reported. Anticipated SAEs due to the underlying disease that do not have to be reported include the following:hospitalisation due to progress of underlying disease;hospitalisation due to bone marrow toxicity of CHT, including:neutropenic fever,anaemia requiring transfusion of red blood cell concentrates,haemorrhagic events necessitating intervention/transfusion due to thrombocytopenia;hospitalisation due to severe nausea, vomiting and exsiccosis caused by CHT;hospitalisation due to severe impairment of hepatic/renal function related to CHT.

The occurrence of pneumothorax and haemothorax will be documented as SAEs for safety reasons.

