#### Further analyses

In addition to the evaluation of the FAS a PP analysis will be performed including all randomised patients without major protocol violations. The secondary variables will be analysed descriptively by tabulation of the measures of the empirical distributions. According to the scale level of the variables, means, standard deviations, medians and first and third quartiles, as well as minimum and maximum or absolute and relative frequencies will be reported. Descriptive *P* values of the corresponding statistical tests comparing the treatment groups and associated 95% confidence intervals will be given.

The homogeneity of the treatment groups will be described by comparison of the demographic data and the baseline values. Statistical methods will be used to assess data quality and the homogeneity of the intervention groups. A safety analysis will be conducted and will include calculation and comparison of frequencies and rates of SAEs. All analyses will be done using SAS version 9.1 or higher (SAS Institute Inc., Cary, North Carolina, USA).

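### The SAE reporting exemption is broader than its stated reason: serious events with both a port and a chemotherapy cause can escape 24-hour reporting, and it is unclear whether exempt events still get an SAE form

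*Protocol article*

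**What the plan says.** Under Safety aspects, from randomisation to day 30 or premature withdrawal, "all SAE will be documented on an SAE form, available in the investigator site file". Assessment "will be carried out by the investigators at the participating trial centres", and of these investigators the article says: "They will be furnished with written recommendations on how to assess the causal connection with trial interventions". On notification: "An SAE will have to be reported to the principal investigator by the attending physician within 24 hours after it becomes known". That section states no exception.

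The next section, Study-specific serious adverse events, introduces one: "only SAEs not related to the underlying disease or treatment will have to be reported". Its example is "hospitalisation due to neutropenic fever after CHT". The list of anticipated events that need not be reported includes, under bone marrow toxicity of chemotherapy, neutropenic fever and "haemorrhagic events necessitating intervention/transfusion due to thrombocytopenia". The section closes by keeping pneumothorax and haemothorax as SAEs. It says nothing similar for infection or bleeding at the port.

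Under Further analyses, the safety analysis includes "calculation and comparison of frequencies and rates of SAEs".

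**The concern.** Exempting expected oncological events is reasonable as long as it removes only events that have nothing to do with the procedure under test. The section gives that as its reason, but the rule asks a different question: whether the event is related to the disease or its treatment. An event can be related to chemotherapy and to the port at once. Two of the named categories, fever in neutropenia and bleeding in thrombocytopenia, are ones in which a port infection or port bleeding could present.

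Two things are at stake. The first is prompt notice to the principal investigator of a serious event that may involve the device or the procedure. The second is the SAE comparison. If exempt events are left out of it, the count in each arm depends partly on how unblinded sites attribute events with two possible causes.

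**Working it through.** No arithmetic applies, since the article gives no rate for the exempt events. The check sets the provisions side by side.

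1. **Reason against rule.** The reason given in Study-specific serious adverse events has two conditions: the event is caused by the disease or its treatment, and it is not related to the trial intervention. The rule has one condition, relation to disease or treatment. Four cases follow:
   - Chemotherapy or disease only: exempt under the reason and under the rule.
   - Port only: reportable under both.
   - Neither: reportable under the rule.
   - Port and chemotherapy together: reportable under the reason, exempt under the rule.

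   Only the last case separates the two, and there the rule goes further than its justification.

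2. **Can the last case occur under the article's own definitions?** Table 1 defines catheter sepsis by two or more criteria, among them temperature over 38.3°C and a white cell count below 4.0 G/L. Neutropenic fever can meet both. The layout leaves open whether positive bacteriology from the port catheter is needed throughout or belongs to the C-reactive protein item alone. Either way, a febrile neutropenic patient with a positive port culture can fit both the exempt list and a Table 1 complication. Port bleeding that needs intervention or transfusion in a thrombocytopenic patient can likewise fit the exempt haemorrhage entry. The Background names chemotherapy as a purpose of these ports, and current chemotherapy is recorded at visit one, so the overlap is foreseeable. Its frequency is not stated.

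3. **Documentation against reporting.** Safety aspects contains two duties: to document all SAEs on a form, and to report an SAE within 24 hours. The exemption uses the verb for reporting. It can therefore be read as an exception to the second duty alone, with all SAEs still documented. The article does not say so, however, and the closing sentence that keeps pneumothorax and haemothorax uses the verb for documentation. A site cannot tell from this text whether an exempt event needs a form, and it is equally unclear whether such events enter the SAE comparison under Further analyses.

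4. **Who decides.** The investigators at the centres assess SAEs. Minimisation of measurement bias states that patients and surgeons cannot be blinded. The article describes no central review of attribution. The written recommendations concern the link to the trial intervention, whereas the exemption turns on the link to disease or treatment.

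5. **What is still captured.** Thirty-day morbidity records wound infection, catheter sepsis, post-operative bleeding and haematoma in the CRF on the day of operation and at day 30, each with a Clavien-Dindo grade and with no exemption for disease or chemotherapy. One gap remains: Table 1 defines post-operative bleeding by reoperation and otherwise lists only haematoma, so port bleeding treated without reoperation and without haematoma fits neither bleeding entry.

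**The case against.** The strongest reply is that the exemption is a deliberate and sensible choice in an oncology population, and that its opening words confine it to events with no link to the intervention. Read with that premise, a port infection or port bleed attributed to the implantation stays reportable. The written causality recommendations may say this expressly, but they are not shown in this condensed article. Serious port infections and bleeding also have a second route, the graded 30-day morbidity record, which is compared descriptively between arms.

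Much of this stands. An event correctly attributed to the port alone is reportable, and the morbidity record is a real safeguard. It does not close the gap. The premise gives the reason, while the rule that sites apply tests something else. The morbidity record is completed on the day of operation and at a day-30 telephone interview, so it gives no 24-hour notice, and the article does not link it to the SAE comparison.

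A reader might infer more than the text supports:
- That serious port events disappear from the trial. They do not, because Table 1 complications are recorded and graded regardless of SAE reporting.
- That the exemption flatly contradicts the rule that all SAEs are documented. One provision concerns documentation and the other reporting, so they can be read together. The fault is ambiguity.
- That a haemothorax in a thrombocytopenic patient could be exempted. The section expressly keeps haemothorax as an SAE, and it is part of the primary endpoint.
- That a number of unreported port-related SAEs can be estimated. That would need a hospitalisation rate, a port-related share and a misattribution rate, none of which the article gives.

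**Conclusion.** The point holds in limited form. As written, the exemption covers SAEs with both a port and a chemotherapy cause, which its own reason does not justify. Such events can miss 24-hour reporting and possibly the SAE comparison, on an unblinded local attribution. Whether exempt events still need an SAE form is unclear.

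The size cannot be given. The documents support neither a count of affected events nor a claim that attribution will in fact differ between arms; they show only that the rule leaves room for it. The primary endpoint and its analysis are untouched. The conclusion rests on the rule being applied as worded and on the unseen causality recommendations not already narrowing it. If they do, the article's wording should be brought into line with them.

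**What to change.** This is a cheap improvement, in two parts.

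1. Reconcile Safety aspects with Study-specific serious adverse events: state whether exempt events are still documented on an SAE form, and which events enter the SAE comparison under Further analyses.
2. Restore the section's own premise to the rule. Suggested text: *The exemption applies only to SAEs with no suspected relation to the trial intervention. Any SAE that may involve the port, catheter, port pocket, access vein or pleural space, including any Table 1 complication that meets the SAE criteria, is documented and reported with a causality rating, whether or not the disease or chemotherapy may also have contributed.*

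The cost is a change of wording in the safety section and a modest number of extra SAE forms. No visit, test or treatment rule changes. Recruitment is under way according to Trial status, so the change would go to the ethics committees as an amendment, a route already described under Ethical and legal aspects.

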### Analysis

#### Hypotheses

The primary endpoint is the occurrence of pneumothorax and haemothorax after implantation of a TIVAP. To formalise the statistical approach, the following notation will be used: p_open_/p_closed_, that is, rate of occurrence of pneumothorax and haemothorax after implantation of a TIVAP in the open-strategy group (open)/closed-strategy group (closed).

The following two-sided test problem is defined:$$ {\mathrm{H}}_0:{\mathrm{p}}_{\mathrm{open}}={\mathrm{p}}_{\mathrm{closed}}\mathrm{versus}\ {\mathrm{H}}_1:{\mathrm{p}}_{\mathrm{open}}\ne {\mathrm{p}}_{\mathrm{closed}} $$

#### Analysis sets

Each patient’s allocation to the different analysis populations (full analysis set (FAS) according to the intention-to-treat (ITT) principle, per protocol (PP) analysis set and safety analysis set) will be defined prior to the analysis. The allocation will be documented in the statistical analysis plan. During the data review, deviations from the protocol will be assessed as ‘minor’ or ‘major’. Major deviations from the protocol will lead to the exclusion of a patient from the PP analysis set.

#### Testing the primary hypothesis

The null hypothesis H0 will be assessed by testing the intervention effect in a logistic regression model that takes into account the covariates ‘intervention’ (open or closed strategy), ‘skill of surgeon’ (board certificate yes or no, number of TIVAP implanted), ‘body mass index’ (kg/m^2^), ‘Karnofsky index’ (percentage) ‘gender’ (female or male) and ‘age’ (years). A two-sided type I error rate of α = 0.05 will be applied. Confirmatory analysis will be primarily based on the FAS, which is consistent with the ITT principle by including all patients randomised to the two groups. This approach reflects the idea that the study should match the conditions in clinical practice as closely as possible.

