### Sample size

A review of the previous literature, including our own randomised controlled trials, revealed a pneumothorax and haemothorax rate of about 3% for placement of a TIVAP by PSV; however, there is no risk if implantation by SCD is successful [14-18]. SCD was successful in 71 to 94% of cases (including the RT), therefore, about 17.5% of patients underwent PSV as a secondary implantation technique. Thus, the overall risk of pneumothorax and haemothorax for the open strategy is about 0.5% (0.175 × 0.03). Assuming a difference of 2.5%, a trial with a desired power of 0.9 and a type 1 error of 0.05 would need to include 577 patients per group to detect this difference in pneumothorax and haemothorax frequency when applying a chi-square test. No missing values for the primary endpoint are assumed, so a total of 1,154 patients have to be randomised into the two intervention groups. A Consolidated Standards of Reporting Trials (CONSORT) flow chart is provided in Figure 1.

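### The 90% power is computed for a chi-square test, but the confirmatory test is a covariate-adjusted logistic model on about 20 expected events; its power is not stated and, under a Wald test, would be about 86–87%

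*Protocol article*

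**What the plan says.** The Sample size section of the protocol article plans on 3% pneumothorax or haemothorax in the closed arm and about 0.5% in the open arm. It concludes that the trial needs "577 patients per group to detect this difference in pneumothorax and haemothorax frequency when applying a chi-square test", with power 0.9 and type 1 error 0.05.

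The section Testing the primary hypothesis uses a different procedure. The null hypothesis is assessed by "testing the intervention effect in a logistic regression model that takes into account the covariates" intervention, skill of surgeon (board certificate, and number of ports implanted), body mass index, Karnofsky index, gender and age, two-sided at 0.05 in the full analysis set. Neither the estimation method nor the test statistic is given. The section Skill of surgeons records experience in four classes: "1 to 10, 11 to 25, 26 to 50 or >50 TIVAP implantations".

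**The concern.** The stated power belongs to a test that will not decide the trial. For a common outcome the gap would hardly matter, but here the planned rates leave about three events in the open arm. The article's own premise, that successful cut-down carries no risk, also makes an empty open arm a foreseeable result. An ordinary logistic fit then has an infinite treatment coefficient. A Wald test would fail to reject exactly when the open strategy performs best. Whether the same data lead to rejection can therefore depend on a choice that the section leaves open.

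**Working it through.** **Inputs.** From Sample size: 3% closed, 0.5% open (0.175 × 0.03 = 0.525%, rounded), 577 per arm, cut-down success 71 to 94%. From Testing the primary hypothesis: the covariate list and two-sided α = 0.05.

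**1. The plan's figure.** With pooled variance and no continuity correction, n = [1.960·√(2p̄(1−p̄)) + 1.282·√(p₁(1−p₁) + p₂(1−p₂))]² / (p₁−p₂)². With p₁ = 0.03, p₂ = 0.005 and p̄ = 0.0175, this is (0.36345 + 0.23657)² / 0.025² = 576.04, so 577 per arm. The figure is reproduced.

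**2. Expected events.** 577 × 0.03 = 17.3 closed and 577 × 0.005 = 2.9 open, 20.2 in all.

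**3. Parameters beyond the intercept.** Intervention 1, board certificate 1, experience 3 (four classes as dummies) or 1 (one term), and body mass index, Karnofsky index, gender and age 4. The total is 9 or 7, which gives 20.2/9 = 2.2 or 20.2/7 = 2.9 events per parameter.

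**4. Unadjusted power at 577 per arm, by exact binomial enumeration.**

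| Rates (closed vs open) | Chi-square | Wald | Likelihood ratio | P(no open-arm events) |
|---|---|---|---|---|
| 3% vs 0.5% | 93.6% | 86.5% | 94.1% | 0.995^577 = 5.5% |
| 3% vs 0.18% (94% success: 0.06 × 0.03) | 99.3% | 63.5% | 99.6% | 0.9982^577 = 35.4% |

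With no open-arm events the maximum-likelihood log odds ratio is infinite and Wald cannot reject. In the second row its power therefore cannot exceed 100 − 35.4 = 64.6%, and the empty arm explains nearly all of the loss. For example, 17 versus 0 events gives a chi-square z of 4.15 and a likelihood-ratio statistic of 23.8 on 1 df, yet no usable Wald test.

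**5. Adjusted model at 3% vs 0.5%, by simulation.** Covariate distributions are assumed. Effects were either none or modest (log-odds 0.2 to 0.7), except for Firth, which was run with none. There were 12,000 replicates per scenario for maximum likelihood and 3,000 for Firth.

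| Test, 9-parameter model | Power | Type I error (1.75% in both arms) |
|---|---|---|
| Wald | 86.5–87.2% | 4.5% |
| Likelihood ratio | 94.1–94.3% | 5.7% |
| Firth, penalised likelihood ratio | 93.0% | 4.7% |

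A separate run of 3,000 replicates, with covariates unrelated to outcome, gave 85.8% for Wald. In the 12,000-replicate runs some coefficient, for treatment or for a covariate level, diverged or failed to converge in about 8–10% of trials. Firth rejected in all 176 of its simulated trials with no open-arm events.

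**6. Source of the loss.** Wald power is 86.5% without covariates and about 86–87% with them. The covariates cost almost nothing; the Wald statistic with about three open-arm events costs the power.

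**The case against.** The strongest reply is that the article names neither maximum likelihood nor Wald. It also refers to a pre-specified statistical analysis plan that is not shown, and a test statistic and the handling of separation are often left to such a plan. That stands: the absence of those details is not itself the finding, and the figures for Wald are conditional.

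A reader might infer more in three ways, and the documents support none of them.

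- **That the planned analysis cannot deliver 90% power.** The likelihood-ratio and Firth tests of the same model both exceed 90% at 577 per arm. The shortfall is specific to Wald and is about 3 to 4 points below 90% at planning rates.
- **That 2 to 3 events per parameter is the cause.** Unadjusted Wald power is the same, and the simulated type I error of the adjusted tests stays near 5%. The coding of experience, and so the count of 9, is also not fixed in the article.
- **That the logistic model tests the wrong hypothesis.** In a randomised comparison with no treatment effect, the conditional odds ratio is 1 and the rates are equal, so the model does address the stated null hypothesis. Nothing prevents a risk difference from being reported as well.

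The 64% also sits at the top of the article's success range; the planning value is a failure rate of 17.5%. What remains is a mismatch between two current sections: the power is calculated for one test and the decision rests on another, whose power is not stated and whose ordinary fit has no finite treatment estimate in about 5% of trials.

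**Conclusion.** The point holds in a limited form and is a should-fix. The 90% power was calculated for an unadjusted chi-square test, and no power is given for the adjusted logistic test that decides the trial. Under ordinary maximum likelihood with Wald, which is an assumption, power is about 86–87% at 3% versus 0.5%, and about 64% (unadjusted) at 94% cut-down success. No finite treatment estimate exists in 5.5% and 35% of trials respectively. Under a likelihood-ratio or Firth test the stated power is kept. The unadjusted figures are exact; the adjusted ones rest on assumed covariate distributions and effects. An analysis plan that already names a suitable test would settle the Wald and separation problem, and the Sample size section would still need to state the power of that test.

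**What to change.** In Testing the primary hypothesis, specify Firth penalised logistic regression, with a penalised likelihood-ratio test and a profile-likelihood confidence interval for the intervention effect. Firth is preferable to the ordinary likelihood-ratio test because it also gives a finite estimate when the open arm is empty, and its simulated type I error was nearer nominal (4.7% against 5.7%). Preferably shorten the covariate list, for example by entering experience as one term (7 parameters instead of 9). Report the risk difference with a 95% confidence interval alongside, since the planning is in rates. In Sample size, state the power for the test actually used.

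Making the chi-square test primary, or a Mantel-Haenszel test stratified by centre to match the randomisation, with the covariate model as supportive, is an acceptable alternative but not a required correction.

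The cost is wording in the analysis section and the analysis plan before database lock, with no further patients or data.
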